**Methods and design:**

GPs and nurses from 24 practices across the North East (n = 12), London and South East (n = 12) of England will be recruited. Practices will be randomly allocated to one of three intervention conditions: a leaflet-only control group (n = 8); brief structured advice (n = 8); and brief lifestyle counselling (n = 8). To test the relative effectiveness of different screening methods all practices will also be randomised to either a universal or targeted screening approach and to use either a modified single item (M-SASQ) or FAST screening tool. Screening randomisation will incorporate stratification by geographical area and intervention condition. During the intervention stage of the trial, practices in each of the three arms will recruit at least 31 hazardous or harmful drinkers who will receive a short baseline assessment followed by brief intervention. Thus there will be a minimum of 744 patients recruited into the trial.

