In addition, there are key gaps in the evidence-base regarding the cost-effectiveness of brief interventions, the efficiency of screening activity and the ideal format of brief intervention. Regarding the cost-effectiveness of screening and brief intervention in primary care, one US study has reported cost-savings from brief alcohol intervention four years after the intervention was delivered [21]. However, it is necessary to establish if similar cost-savings can be found in different research trials and different country contexts. Also, despite the fact that the vast majority of trials in this field have involved screening to identify patients who require brief intervention, the efficiency and acceptability of screening has been questioned [22,23]. In particular, doubts have been expressed about the strategy of screening all patients (universal screening) and it has been suggested that clinicians should only screen patients with a high likelihood of alcohol-related problems [24]. However, such targeted screening has not been evaluated in terms of either its effectiveness or efficiency in primary care. Lastly, although brief intervention can result in positive changes in excessive drinking, it is not clear if simple structured advice is sufficient for all hazardous and harmful drinkers or if motivationally enhanced counselling provides significant additional benefit to some individuals. The most recent review of brief alcohol intervention found no significant additional benefit of longer compared to shorter brief interventions [17]. However, this meta-regression analysis focused on the length of time clinicians spent delivering brief intervention to patients and not the content of the brief intervention sessions. Simple, structured advice may take less time to deliver and involve less preparatory training but it may also have less impact than motivationally-enhanced counselling. Thus there is a clear need for both an impact and cost-effectiveness analysis of differing intensities of brief alcohol intervention.

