### Inclusion criteria

#### Practices

All practices delivering general medical services who have not already instigated screening and brief intervention systems.

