### Interventions

#### Patient Information Leaflet

In the eight practices randomised to the control condition, participating staff will be trained to screen eligible patients for hazardous or harmful drinking. Patients who screen positive and provide consent to participate in the study will complete the baseline questionnaire and then be provided with a patient information leaflet (PIL) . The PIL to be used in this trial is the Department of Health's 'How much is too much? Drinking and you' which contains details of the Drinkline telephone number where the patient can access further information including treatment options for alcohol problems. A sticker with local alcohol services will also be attached to the back cover.

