### Economic evaluation

The economic component of the study will consist of a cost-effectiveness and cost-utility analysis. The study aims to identify, quantify and value resources related to alcohol SBI by clinicians in primary care and the subsequent use of health, social care and criminal justice services by patients following each type of intervention.

Resources utilised in the identification and brief intervention delivery or control condition will be recorded by practice staff involved on an ongoing basis. This will allow the calculation of costs of implementation of different models of screening and brief intervention. Local values will be used to calculate the costs of the interventions, which will include staff costs, premises costs and costs of leaflets and other consumables. In addition, specific training costs for staff will be calculated, in terms of staff time, premises costs and the cost of training materials.

Patients' use of health, social care and criminal justice services will be identified retrospectively using a short SUQ and applying a common set of national unit cost estimates. Patient costs in the 6 month period before SBI can then be compared to cost in the 6 month period after SBI to explore any changes in costs imposed by patients in each group.

The economic analysis will calculate the incremental cost-effectiveness of the control condition with each of the screening and brief intervention conditions under study, using measures of clinical outcome and quality of life responses at 6 and 12 month follow-ups. The use of EQ-5D enables the estimation of Quality Adjusted Life Years (QALYs). Data will be bootstrapped to account for the expected skewness evident in economic cost data [46]. The analysis will include the construction of cost-effectiveness acceptability curves to illustrate the probability that the brief intervention is more cost-effective than usual care, based on different monetary values being attached to QALYs. The use of QALYs follows the recommendations of NICE [47] and enables the value for money afforded by treatment to be compared to a range of other health care interventions. Furthermore, combination of the economic cost data and outcome data with patient data collected in the trial will enable a secondary analysis of various patient characteristics that may influence the cost-effectiveness of the intervention.

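### The economic plan names usual care, which is not a trial arm, as the comparator for its acceptability curves and states no counselling-versus-advice comparison

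*Protocol article*

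**What the plan says.** The Economic evaluation section fixes three things. The incremental analysis is set against control: "The economic analysis will calculate the incremental cost-effectiveness of the control condition with each of the screening and brief intervention conditions under study". The acceptability curves use a different label and a single active option; they are to "illustrate the probability that the brief intervention is more cost-effective than usual care". Uncertainty is handled by resampling, with one stated reason: "Data will be bootstrapped to account for the expected skewness evident in economic cost data".

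The Abstract lists the arms as "a leaflet-only control group (n = 8); brief structured advice (n = 8); and brief lifestyle counselling (n = 8"). Under Patient Information Leaflet, control patients who screen positive and consent will "complete the baseline questionnaire and then be provided with a patient information leaflet (PIL"). Under Brief lifestyle counselling, patients in that arm receive the brief advice and the leaflet, and a 20-minute counselling session is offered at a later appointment.

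The section on current evidence ends its case for the trial with: "Thus there is a clear need for both an impact and cost-effectiveness analysis of differing intensities of brief alcohol intervention". The Abstract background likewise promises to evaluate cost-effectiveness across intensities of brief intervention.

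**The concern.** Two features of the stated analysis do not fit the design or its rationale.

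First, the comparator of the curves is not an arm of the trial. Screening takes place in every arm, so its cost largely cancels in any contrast with the leaflet arm. A curve labelled with usual care invites a commissioner to read it as the value of introducing screening and brief intervention where there was none. What the trial estimates is the value of adding advice or counselling to screening plus a leaflet. Speaking of one brief intervention also fits poorly with two active arms.

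Second, the three options rise in intensity and the most intensive contains the middle one. A ratio of counselling against leaflet therefore includes whatever advice achieves. Whether counselling is worth its extra cost over advice is the question the background raises, and the analysis as written does not name the contrast that answers it.

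**Working it through.** The article states no ratio, QALY gain, cost by arm or willingness-to-pay value, so there is no figure of the plan's own to reproduce. The check is one of text, followed by an illustration.

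**1. Comparator.** Economic evaluation first names the control condition, then usual care for the curves. The three arms are leaflet, advice and counselling. Eligible practices are "All practices delivering general medical services who have not already instigated screening and brief intervention systems", so usual care there would include no such system. The leaflet control, which is screened, assessed and given a leaflet, cannot simply be equated with it.

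**2. Purpose against planned contrasts.**
- Abstract background and the current-evidence section: cost-effectiveness of different intensities.
- Objectives: models of brief intervention compared with a control condition.
- Study Hypotheses: effectiveness is ordered across all three arms; cost-effectiveness is set as advice or counselling against leaflet.
- Economic evaluation: control with each condition.

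The planned contrasts match the formal objective and the cost-effectiveness hypothesis. The mismatch is with the stated rationale.

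**3. What ratios against a common control can hide.** Let C and Q be extra cost and QALY gain over leaflet. Then

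counselling v leaflet = C_BLC / Q_BLC

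counselling v advice = (C_BLC − C_BA) / (Q_BLC − Q_BA)

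The first ratio is the average of the advice-v-leaflet and counselling-v-advice ratios, weighted by QALYs gained at each step. A cheap first step can therefore mask an expensive second one.

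Assumed inputs, none from the document: C_BA = £8, C_BLC = £40, Q_BA = 0.002, with Q_BLC varied. Advice v leaflet is 8/0.002 = £4,000 per QALY throughout.

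| Q_BLC | Counselling v leaflet | Counselling v advice |
|---|---|---|
| 0.004 | 40/0.004 = £10,000 | 32/0.002 = £16,000 |
| 0.0025 | 40/0.0025 = £16,000 | 32/0.0005 = £64,000 |
| 0.002 | 40/0.002 = £20,000 | 32/0: no ratio; costs more, no gain |

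Check on the middle row: (0.002 × 4,000 + 0.0005 × 64,000)/0.0025 = (8 + 32)/0.0025 = £16,000.

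Across the three rows the ratio against leaflet only doubles, while the ratio against advice goes from £16,000 to dominated.

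**4. Can the trial supply the comparison?** EQ-5D and service use are collected at baseline and follow-up in all arms, and delivery resources are recorded by practice staff. The counselling-v-advice increments in cost and in QALYs are the differences between the two planned contrasts with control. The data suffice.

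**The case against.** The strongest reply is that this is loose wording in a condensed article. The same paragraph names the control condition as comparator, and the cost-effectiveness hypothesis names the leaflet, so usual care probably means the leaflet arm. Nothing in the text excludes a counselling-v-advice comparison, and a fuller economic plan may contain one. The plan also follows its own objective and hypothesis.

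Much of this stands, and it rules out three stronger readings.

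- A reader might infer that the trial cannot say whether counselling is worth its cost over advice. It can, from data already planned.
- A reader might infer that an analysis against a missing arm is intended. The surrounding text points to a labelling inconsistency.
- A reader might infer that the bootstrap will resample patients and ignore practices. The article gives no resampling unit. If it did so, and if costs and QALYs shared the ICC of 0.04 used in the sample size, the design effect would be 1 + (23.25 − 1) × 0.04 = 1.89 after 25% loss, or 1 + 30 × 0.04 = 2.2 without loss. Nominal 95% intervals would then cover about 85% or 81%. Both conditions are assumptions, so no error is shown.

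The reply does not remove the printed comparator, which is wrong for this design. Nor does it change the fact that the contrasts actually stated are all with control, while the background asks about intensity.

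**Conclusion.** The point holds in limited form. As written, the economic plan labels its acceptability curves with a comparator the trial does not have, and it names no counselling-versus-advice comparison although cost-effectiveness by intensity is a stated purpose. Followed literally, it could present counselling favourably against the leaflet when most of the benefit comes from the advice it contains.

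The size in this trial cannot be derived. The contrast of £16,000 with £64,000 per QALY rests wholly on assumed costs and gains and shows only that such masking is possible. This concerns a secondary, economic analysis and leaves the primary drinking outcome untouched. How the bootstrap treats practices is something to specify, not a demonstrated fault.

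**What to change.** In Economic evaluation:

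1. Replace usual care with the screening-plus-leaflet control.
2. State a full incremental analysis of leaflet, advice and counselling: order the options by cost, remove dominated options, and compute each ratio against the next best remaining option, with counselling v advice named explicitly.
3. Present one acceptability curve showing all three options together.
4. State that the bootstrap respects the randomised unit, for example by resampling practices within arm and then patients, keeping each patient's cost and QALY paired.

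The cost is modest analysis work and revised wording, with no new data. The counselling-v-advice ratio will be less precise than ratios against leaflet, because the increments are likely to be smaller while the number of practices per arm stays at eight. Intervals that respect practices may also be wider.

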### Sample size calculation

The sample size calculation was designed to account primarily for intervention level outcomes. Powering the study in this way will also account statistically for appropriate outcomes for screening approach and screening method. The primary outcome for this study is the proportion of patients who consume alcohol within recommended levels at 6 month follow up. A comprehensive meta-analysis [13] suggested that the difference between brief intervention and control is of the order 13%; that is a 5% reduction in the control group and 18% in the brief intervention group. Detecting a difference of this magnitude at the 5% significance level with 80% power, for a 2-sided test, requires 109 patients in each of the 3 groups and a total of 327. Our experience with other multi-centre randomized controlled trials of interventions for alcohol use disorders suggests that with assiduous follow-up the potential loss to follow-up across groups is of the order 25%. Taking this loss into accounts inflates the sample required to 145 in each group, a total of 435 patients.

The proposed study involves a cluster design and requires a statistical adjustment to account for any potential cluster effect. The literature, and our previous experience of trials in primary care [44], suggest an intra-class correlation coefficient of 0.04 is appropriate. Assuming a cluster size of 31 patients inflated the sample size calculation by a factor of 1.7 requiring 248 patients in each group and a total of 744, with an expectation that at least 558 will be followed up at 12 months.

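### The clustering factor of 1.7 does not follow from an ICC of 0.04 and 31 patients per practice; at 1.89, the 744 patients give about 75% power, not 80%, by the formula behind the plan's 109

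*Protocol article*

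**What the plan says.** All the inputs are in the protocol article under Sample size calculation.

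- Effect: a 13-point difference, "that is a 5% reduction in the control group and 18% in the brief intervention group".
- Error rates: "at the 5% significance level with 80% power, for a 2-sided test".
- Patients before any inflation: the plan "requires 109 patients in each of the 3 groups and a total of 327".
- Attrition: "the potential loss to follow-up across groups is of the order 25" per cent, which "inflates the sample required to 145 in each group, a total of 435 patients".
- Clustering: the literature and previous experience "suggest an intra-class correlation coefficient of 0.04 is appropriate".
- Result: "Assuming a cluster size of 31 patients inflated the sample size calculation by a factor of 1.7 requiring 248 patients in each group", a total of 744, of whom at least 558 are expected at 12 months.

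The Design section fixes 8 practices per intervention arm (8 × 31 = 248). The abstract repeats the total: "Thus there will be a minimum of 744 patients recruited into the trial". No other ICC, cluster size or inflation formula appears in the article.

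**The concern.** The ICC, the cluster size and the factor appear in consecutive sentences and do not agree. The factor turns 145 per group into 248, so the total of 744 and the claim of 80% power both depend on it. The same section relies on this calculation to cover the screening comparisons, and the Design section says that each factor can be analysed with sufficient power. If the three interventions turn out not to differ significantly, readers will judge that result against a stated 80% power that the plan's own inputs do not give.

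**Working it through.** **1. Before clustering (reproduces).** For 5% v 18%, d = 0.13 and the mean proportion is 0.115. With z = 1.960 and 0.842:

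n = [1.960 × √(2 × 0.115 × 0.885) + 0.842 × √(0.05 × 0.95 + 0.18 × 0.82)]² / 0.13² = 93.3.

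With the continuity correction, n′ = (n/4) × [1 + √(1 + 4/(n × d))]² = 108.2, rounded up to 109. The plan's 109 is therefore the continuity-corrected figure; without the correction it would be 94.

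**2. Loss to follow-up (reproduces).** 109 / 0.75 = 145.3, printed as 145.

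**3. Clustering (does not reproduce).** Design effect = 1 + (m − 1) × ICC, with ICC = 0.04.

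| Cluster size m | Design effect |
|---|---|
| 31 (recruited) | 1 + 30 × 0.04 = 2.20 |
| 31 × 0.75 = 23.25 (followed up) | 1 + 22.25 × 0.04 = 1.89 |
| 145 / 8 = 18.1 | 1 + 17.1 × 0.04 = 1.69 |

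The printed factor is not a misprint: 145 × 1.7 = 246.5, and 248 / 145 = 1.71. At ICC 0.04, a factor of 1.7 needs m = 1 + 0.7/0.04 = 18.5.

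**4. What 744 patients deliver.** Expected follow-up is 558 / 3 = 186 per arm, or 23.25 per practice. The factor that matches these patients is 1.89.

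- With the printed factor: 186 / 1.7 = 109.4, which is how the plan appears to meet its 109.
- With 1.89: 186 / 1.89 = 98.4, short of 109.

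Power at an effective 98.4 per arm:

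| Method | Power |
|---|---|
| Continuity-corrected formula (the one giving 109) | 75% |
| t distribution, 14 df (2 × 8 − 2), SE = √(0.1951/98.4) = 0.0445, non-centrality 0.13/0.0445 = 2.92 | 77% |
| Simulated cluster-level t-test, 8 practices of 23 per arm, ICC 0.04 | 79% |
| Normal approximation, no correction | 82% |

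**5. What 80% would need on the plan's formula.** 109 × 1.89 / 0.75 = 274.7, so about 275 per arm and about 824 in total (3 × 274.7). This keeps 31 per practice, so it implies more practices: 274.7 / 31 = 8.9, or 9 per arm.

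**The case against.** The strongest case on the other side is that the consequence is small and depends on the method. The article never names a continuity correction; it is inferred because it reproduces 109. The planned primary analysis is logistic regression, which does not use one. At a design effect of 1.89, ordinary alternatives give 77% to 82%, so 744 patients come close to 80% or exceed it. This stands as a limit on the size of the problem. It does not repair the factor, because no choice of test makes 0.04 and 31 yield 1.7. It also sets aside the method that evidently produced the plan's 109.

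A second objection is that 31 is a minimum per practice, so recruitment could exceed 744. That helps little, since the Financial incentives section lets practices stop at the minimum.

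Two stronger readings are tempting, and the document does not support them. A reader might apply 2.20 throughout and infer 145 × 2.2 = 319 per arm (957 in total), or 186 / 2.2 = 85 effective patients and 68% power. This prices clustering on 31 analysed patients per practice while counting only the 23.25 followed up, so it overstates the shortfall. A reader might also infer from 145 / 8 = 18.1 that the authors used the cluster size from before clustering inflation. That fits numerically, but the article does not say so, and the point does not need it.

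**Conclusion.** The factor 1.7 is wrong for the stated inputs under either usual reading of cluster size. With the factor that matches the patients followed up, 1.89, the effective sample is about 98 per arm against 109. The stated 80% becomes about 75% on the plan's own formula, and 77–82% by other ordinary methods. This is an error in the planning statement with a modest effect on power. It does not show that the trial is seriously underpowered.

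The conclusion rests on four assumptions: the plan's ICC of 0.04; equal practice sizes; 25% loss spread evenly across practices; and the same loss at the 6-month primary endpoint. On the last, the article gives the 558 only for 12 months. Better retention would narrow the gap. With no loss at all, 248 / 2.20 = 112.7 would exceed 109.

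**What to change.** In Sample size calculation, replace 1.7 with 1.89. State that it is 1 + (23.25 − 1) × 0.04, computed on patients followed up per practice, and name the continuity-corrected two-proportion formula behind 109. Keep 24 practices of 31 patients. Present 248 per arm as what 8 practices supply, not as what 80% power requires. Restate the power for 5% v 18% as about 75% on that formula, and 77–82% by the other methods above.

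Leave the ICC at 0.04. The section says it comes from the literature and earlier trials, and choosing a smaller value now so that 1.7 comes out would fit the input to the answer.

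The cost is wording only, with a less favourable power statement. The 744 in the abstract and Table 1, the allocation and the analysis do not change.

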### Planned analysis

As the study is pragmatic in design, the planned analysis will be by intention to treat. The primary outcome (drinking within or above recommended levels) is dichotomous and so will be analysed with logistic regression adjusting for all known prognostic factors; data will be presented as odds ratios and their corresponding confidence intervals. Secondary analyses will be undertaken using the appropriate method for the outcomes, controlling where appropriate for intake values and other known prognostic variables using analysis of covariance. Due to the nested factorial nature of the study, we will use multi-level modelling to explore potential interactions between each of the three levels nested within the trial (screening approach, screening method and intervention). Practice and patient factors will be utilised as part of regression model to explore possible prognostic factors that impact on outcome. Interaction analysis will explore any possible interactions between practice and patient characteristics and outcome. The efficacy of interventions will be explored with a secondary analysis utilising a per protocol approach; a sub-sample of patients who engaged in their allocated treatment will be utilised in this analysis.

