### Design

The trial has a 2 × 2 × 3 nested factorial design encompassing screening approach (targeted versus universal screening), screening method (the Fast Alcohol Screening Test (FAST) [25] or a modified Single Alcohol Screening Questionnaire (M-SASQ)) [26]) and brief intervention intensity (Patient information leaflet (PIL); Brief advice (BA); Brief lifestyle counselling (BLC)). The main advantages of utilising a factorial approach are twofold. First each of the three elements (screening approach, screening tool and intervention) can be analysed independently with sufficient power to make meaningful interpretation of relative effectiveness. Second, the method enables meaningful interpretations of the relative effectiveness of any combination of screening approach, screening tool and intervention modality.

We will recruit 24 general practices from the North East, London and the South East of England. Practices will be randomly assigned to 1 of 2 screening approaches (12 practices in each approach), 1 of 2 screening tools (12 practices using each tool) and 1 of 3 intervention conditions (8 practices in each condition) as shown in Table 1. Since we expect that there may be a difference in uptake of screening between intervention conditions, we expect the recruitment to take varying periods of time in the different conditions.

**Table 1 T1:** SIPS Primary Care trial design

**Intervention condition**		North			London & the South East			
**Screening condition**		Leaflet	Brief Advice	Brief Counselling	Leaflet	Brief Advice	Brief Counselling	Totals

Targeted presentation	FAST	31	31	31	31	31	31	186 (6)
	M-SASQ	31	31	31	31	31	31	186 (6)
Universal presentation	FAST	31	31	31	31	31	31	186 (6)
	M-SASQ	31	31	31	31	31	31	186 (6)

Number of patients per intervention		124	124	124	124	124	124	744
Number of practices per intervention		4	4	4	4	4	4	24

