The trial will incorporate cluster randomisation of practices to avoid the risk of contamination. Clinicians trained to deliver 'talk-based' advice or counselling become compromised in their ability to deliver alternative versions of such care; thus it is not practical for individual clinicians to deliver both control and intervention conditions in this trial. Therefore clinicians will consistently deliver a particular version of brief intervention. Cluster randomisation also provides an opportunity to pragmatically evaluate brief interventions in primary care in a way that will allow issues of implementation to be addressed from a practice perspective.

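### The primary logistic regression is stated without allowance for practice clustering; if fitted as a single-level model, a nominal 5% test would have about 15% type I error

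*Protocol article*

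**What the plan says.** The Design section makes the practice the unit of allocation: "The trial will incorporate cluster randomisation of practices to avoid the risk of contamination". There are 24 practices, eight in each of the three intervention conditions.

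The Sample size calculation section recognises the consequence: "The proposed study involves a cluster design and requires a statistical adjustment to account for any potential cluster effect". It takes an intra-class correlation of 0.04 and a cluster size of 31, and inflates the sample by 1.7 to 248 per group and 744 in total. At least 558 patients are expected to be followed up.

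The Planned analysis section then says that the primary outcome "is dichotomous and so will be analysed with logistic regression adjusting for all known prognostic factors", reported as odds ratios with confidence intervals. A later sentence brings in a hierarchical method for a different purpose: "we will use multi-level modelling to explore potential interactions between each of the three levels nested within the trial", these being screening approach, screening tool and intervention. Practice and patient factors also enter a regression model, to explore prognosis.

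**The concern.** The design and sample size sections treat the practice as the source of correlated outcomes. The sentence that fixes the primary model does not. The one hierarchical method in the section is assigned to exploring interactions among three factors that Table 1 shows to be fully crossed, and not to the main intervention comparison.

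A reader who carries out the stated primary analysis literally would fit a patient-level model that treats 558 patients as independent. The intervention effect is a between-practice contrast with eight practices per arm. Ignoring that makes the confidence intervals of the headline odds ratios too narrow and their p-values too small. The sample would have been enlarged for clustering while the test made no allowance for it.

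**Working it through.** **Inputs (all from the protocol article).** 24 practices, eight per arm (Design). Two-sided 5% level, 80% power, 5% versus 18%, 25% loss to follow-up, intra-class correlation 0.04, cluster size 31, factor 1.7, 558 followed up (Sample size calculation).

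**1. Reproduce the plan's own figure.** For 5% versus 18% (mean 0.115, difference 0.13):
- Uncorrected n = [1.96 × √(2 × 0.115 × 0.885) + 0.8416 × √(0.05 × 0.95 + 0.18 × 0.82)]² / 0.13² = 93.4, so 94.
- With continuity correction: (93.4/4) × [1 + √(1 + 4/(93.4 × 0.13))]² = 108.2, so 109. This matches the stated 109 per group.
- Loss to follow-up: 109/0.75 = 145.3 (stated 145). Times 1.7 = 247, which fits 248 = 8 × 31.

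**2. Patients analysed per practice.** 744 × 0.75 = 558, and 558/24 = 23.25. The article gives 558 for 12 months. I assume the same 25% loss at 6 months, when the primary outcome is measured.

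**3. Design effect**, DE = 1 + (m − 1) × ICC:
- m = 23.25: 1 + 22.25 × 0.04 = 1.89
- m = 31: 1 + 30 × 0.04 = 2.20
- the plan's own factor: 1.70

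The plan's 1.7 does not follow from 0.04 and 31. That is a separate matter, and 1.7 is used here only as a lower case.

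**4. Effect of a single-level fit.** The standard error is understated by the factor 1/√DE. At DE = 1.89 this is 0.727, so it is 27% too small. The type I error of a nominal 5% pairwise test is 2 × [1 − Φ(1.96/√DE)]:

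| Design effect | Type I error |
|---|---|
| 1.70 | 13.3% |
| 1.89 | 15.4% |
| 2.20 | 18.6% |

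**5. Sensitivity to the intra-class correlation** (23.25 analysed per practice):

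| ICC | 0.01 | 0.02 | 0.03 | 0.04 | 0.05 | 0.06 |
|---|---|---|---|---|---|---|
| Type I error | 7.6% | 10.3% | 12.9% | 15.4% | 17.7% | 20.0% |

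**6. Check by simulation.** Beta-binomial outcomes, two arms of eight practices, ICC 0.04, no true difference, 200,000 runs per setting. Each cell gives the single-level log-odds-ratio test, then a practice-level t-test on 14 degrees of freedom:

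| Event rate | 23.25 per practice | 31 per practice |
|---|---|---|
| 5% | 12.5% / 4.4% | 16.8% / 4.4% |
| 11.5% | 14.9% / 4.7% | 18.3% / 4.9% |
| 18% | 15.2% / 4.9% | 18.6% / 5.0% |
| 50% | 16.5% / 5.1% | 19.3% / 5.1% |

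The closed formula and the simulation agree, apart from a lower figure at the 5% event rate. An analysis that respects the practice stays at or near the nominal level throughout.

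**The case against.** The strongest reply is that the text is silent rather than wrong. It never calls the logistic regression ordinary or single-level, and never says that clustering will be disregarded. A mixed-effects or GEE logistic model is still logistic regression and still yields odds ratios with confidence intervals. The authors acknowledge the need for adjustment and plan multi-level modelling in the same paragraph, where practice would be the natural upper level. The full protocol or an analysis plan, neither of them shown, may settle the matter.

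Much of this stands. A reader might infer that the trial will be analysed by ordinary logistic regression and that its true type I error is 15%. The document does not support that as a statement of fact. The 15% also depends on the residual correlation. The article does not say whether 0.04 is before or after covariate adjustment, and the planned practice covariates could lower it.

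A reader might also extend the point to the secondary outcomes and to the economic analysis, where "Data will be bootstrapped to account for the expected skewness evident in economic cost data" gives skewness as the reason for resampling. Those passages are brief and do not state the modelling or resampling unit. An absence there is what a condensed article leaves out and is no ground for this point. Nor is the loose use of the word for levels.

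The reply does not remove the core. The article does not leave the primary model open: it names one and gives what it adjusts for. It also names a hierarchical method and assigns it elsewhere. Measured practice covariates do not replace a practice variance term. The primary-analysis sentence therefore does not carry out the adjustment that the sample size section calls for.

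**Conclusion.** The point holds in conditional form. As stated, the primary analysis makes no allowance for the randomised unit, which is inconsistent with the sample size section. If it is fitted single-level, type I error for one pairwise comparison is about 15%. This rests on an intra-class correlation of 0.04, about 23 analysed per practice and equal practice sizes. At that correlation the range is about 12% (5% event rate, 23 per practice) to 19% (31 per practice); at 0.01 to 0.02, with 23 per practice, it is about 8% to 10%. If the model used does account for practice, the error is close to 5% and only the wording is deficient.

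**What to change.** State in the Planned analysis section that the primary outcome will be analysed by a mixed-effects logistic model with a random effect for practice, or by GEE clustered on practice with a small-sample correction. Include fixed effects for intervention, screening approach, screening tool and region. Base inference on the number of practices. With an intercept, two intervention terms and one term each for approach, tool and region there are six parameters, so 24 − 6 = 18 between-practice degrees of freedom and a critical t of 2.10 instead of 1.96.

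The cost is a sentence or two and minor programming. Confidence intervals will be wider than from a single-level fit, correctly so. If an existing analysis plan already specifies such a model, one sentence in the protocol pointing to it is enough.
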